## Abstract

**Background:**

Diabetic nephropathy (DN) is a major microvascular complication with diabetes. In China, an estimated 34.7 percent of people diagnosed with diabetes have renal complications and a further 50 percent die of renal failure. Hence, identification of alternative treatments for these patients should be given priority. The Shenyan Kangfu tablet (SYKFT) is a new formulation of an existing and widely acclaimed Chinese herbal tea for treating qi-yin deficiency syndrome. Because a considerable portion of DN patients presenting with symptoms of swelling, fatigue and weak limbs would be diagnosed with qi-yin deficiency syndrome according to the traditional Chinese medicine (TCM) diagnostic criteria, we hypothesize that SYKFT may represent a complementary drug for DN patients with the corresponding syndrome. In view of this, we have designed a trial to assess the efficacy and safety of SYKFT for patients with diabetic nephropathy exhibiting signs of qi and yin deficiency.

**Methods:**

This is a multicenter, double-blind, randomized controlled trial (RCT). The total target sample size is planned at 80 participants, with a balanced (1:1) treatment allocation. The experimental intervention will be SYKFY plus irbesartan (SI regimen) and the control intervention will be a placebo plus irbesartan (PI regimen). Participants will receive two courses of medication treatment each lasting 8 weeks. The primary outcome will be the composite of the quantitative 24-hour urinary protein level and urinary albumin excretion rate (UAER). Changes in urine albumin-to-creatinine ratio (UACR) and DN staging, and TCM symptom improvement will be the secondary outcome measures. Adverse events (AEs) will be monitored throughout the trial.

**Discussion:**

This study will be the first placebo-controlled RCT to assess whether SYKFT plus irbesartan will have beneficial effects on enhancing overall response rate (ORR), changing DN staging, improving clinical symptoms, and reducing the frequency of AEs for DN patients with qi-yin deficiency syndrome. The results of this trial will help to provide evidence-based recommendations for clinicians.

**Trial registration:**

Chinese Clinical Trials Register, Identifier: ChiCTR-TRC-12002182

## Background

Diabetic nephropathy (DN) is renal disease or damage that occurs in patients with diabetes [1]. The World Health Organization defines it as a major microvascular complication with diabetes, and a leading cause of dialysis and kidney transplant in developed countries [2]. The American National Diabetes Fact Sheet 2011 found DN was liable for 44 percent of new cases of renal failure in 2008 in the United States [3]. According to a national survey conducted in 2007 and 2008, China has the world’s largest diabetic population, with more than 92.4 million people affected [4]. The survey also linked 34.7 percent of the Chinese type II diabetic patients with kidney complications [4]. Moreover, the Chinese National Blueprint for Diabetes Prevention and Control 2011 attributed the deaths of half of all diabetes patients complicated with kidney diseases to renal failure [5]. Early intervention is of profound significance to mitigating clinical symptoms, managing proteinuria and hematuria, slowing disease progression and preventing life-threatening kidney failure.

Currently, conventional treatments for DN include lifestyle changes, dietary protein restriction as well as blood pressure and blood glucose control. Antihypertensives and drugs to reduce proteinuria, such as angiotensin-converting enzyme inhibitors (ACEIs) or angiotensin receptor blockers (ARBs), are recommended renoprotective medications for DN sufferers [4]. However, effective as they are, research finds long-term medication use may lead to a number of adverse reactions such as cough, hypotension, hyperkalemia, exacerbated kidney function and also have negative effects on the fetus [6]. As a result, focus has been shifted from western medicine to traditional Chinese medicine (TCM) for an effective integrated approach to DN, with prospectively low expenses and minimum undesired effects.

It is well known that traditional Chinese medicine cures ailments on the basis of the signs and symptoms of a patient [7]. This means the same group of symptoms is likely to be remedied with the same herbal formula, regardless of the disease type (*Bian zheng lun zhi* in Chinese pinyin), a therapeutic rule derived from the wisdom of the Han dynasty herbalist Zhang Zhongjing (A.D. 150 to 219) [7]. Shenyan Kangfu tablets (nephritis recovery tablets, literally, hereafter referred to as SYKFT) is a Chinese patent drug originally designated for clinical treatment of chronic nephritis patients diagnosed with qi-yin deficiency syndrome (a TCM syndrome characterized by the lack of qi and yin energy in the body) [8]. SYKFT has been considered for use in DN treatment because DN patients may share the same TCM syndrome and clinical symptoms with nephritis sufferers. For instance, they may both display symptoms of mental and physical fatigue, swollen face and limbs, sore waist and weak limbs or dizziness and tinnitus, and may both present a red tongue with little coating and a sunken and string-like/thready pulse upon TCM tongue and pulse diagnosis. Moreover, patients suffering from both diseases may develop proteinuria and hematuria with the progression of renal insufficiency. Thus we speculate that the effective solution for the treatment of nephritis may play a similar role in the treatment of DN. We will conduct a multicenter, double-blind randomized clinical trial (RCT) of SYKFT in phase III and IV DN patients to test this hypothesis.

### Objectives

This clinical trial aims to assess whether Shenyan Kangfu tablets combined with irbesartan (SI regimen) is superior to a placebo combined with irbesartan (PI regimen) in efficacy and safety for DN patients with qi-yin deficiency syndrome.

## Method

### Study design

This is a multicenter, randomized, double-blind and placebo-controlled clinical trial lasting 16 weeks. The design of the trial integrates strict and scientific clinical research methodology in compliance with principals laid down in the Declaration of Helsinki and the Guidelines for Good Clinical Practice (Figure 1).

**Figure 1 F1:**
[figure not shown]
Study flow chart.

### Setting

Participants will be enrolled at five trial sites in four cities in mainland China: 1) Longhua Hospital of Shanghai University of TCM; 2) The Sixth People's Hospital of Shanghai; 3) Guangxing Hospital Affiliated to Zhejiang University of TCM; 4) The First Affiliated Hospital of Tianjin University of TCM and 5) The Affiliated Hospital to Liaoning University of TCM.

### Participants

The study plans to enroll 80 patients diagnosed with diabetic nephropathy and qi-yin deficiency syndrome. They should also meet the items of both the inclusion and exclusion criteria presented in a following section.

### Study criteria

#### Diagnostic criteria

##### Diagnostic criteria for DN

Stage III: early-stage diabetic nephropathy. Urinary albumin excretion rate (UAER) falls within the range of 20 to 200 ug/min or 30 to 300 mg/24h, accompanied by slightly elevated blood pressure.

Stage IV: also termed clinical or dominant diabetic nephropathy. This stage is featured by a large amount of proteinuria, UAER >200 ug/min or the urinary protein quantitative is persistently higher than 500 mg/24h, and it is nonselective proteinuria. Some may present elevated blood pressure and symptoms of nephrotic syndrome.

##### Diagnostic criteria for TCM syndrome differentiation

According to the Guidelines for Clinical Research of Chinese Medicine (New Drug) [9], a patient ought to be currently displaying all the primary symptoms and at least two of the several secondary symptoms listed below to be diagnosed with qi-yin deficiency syndrome.

•Primary signs and symptoms include thirst, increased food and water consumption, excessive hunger and excessive urination at night.

•Secondary symptoms involve exhaustion, fatigue, sore waist, weak legs, swelling face and limbs, dizziness, tinnitus, shortness of breath, tiredness of speaking, sore throat, dry mouth, cold extremities, being upset, insomnia, low-grade fever in the afternoon and feverish palms and soles.

•Tongue and pulse: red tongue with little fur and thready or weak pulse.

### Eligibility and ineligibility criteria

#### Inclusion criteria

•Men and women aged 35 to 65 years.

•Diagnosis of diabetic nephropathy, stage III to IV.

•TCM diagnosis of qi-yin deficiency syndrome.

•Provision of written informed consent by participants or surrogates.

#### Exclusion criteria

•Diagnosis of kidney cancer or other types of renal damage.

•Presence of complications that might affect observation on the curative effects of the test drug.

•Uncontrolled hypertension (blood pressure being persistently greater than 140/90 mmHg).

•Diagnosis of type 1 diabetes mellitus.

•Presence of urinary tract infection.

•Glycated hemoglobin (HbA1c) >59 mmol/mol.

•Twenty-four-hour urinary protein >3 g, serum albumin (ALB) <25 g/L and glomerular filtration rate (GFR) <60 ml/min.

•Presence of serious primary hepatic, pulmonary, hematologic or cardiovascular diseases or any other life-threatening conditions.

•History of allergy to TCM products.

•Recent participation in another clinical trial.

•Pregnancy, lactation or those who are preparing for pregnancy.

### Other criteria

#### Concomitant treatments and forbidden drugs

•Use of any other Chinese medicine or western therapy like ACEIs or ARBs to relieve symptoms of diabetic nephropathy ought to be strictly prohibited.

•Use of medication to control other conditions of the patients, such as anticoagulatory or lipid-lowering drugs, is allowed.

•Details of any additional drug or therapy taken must be recorded in the case report form (CRF). These include drug name, dose and treatment duration.

Early suspension or termination of the trial will occur in the following situations:

•Occurrence of serious adverse events, flawed protocol or significant deviation in implementation.

•Funding or management problems.

•The administrative authorities decide to terminate the study.

Patients will be withdrawn or be rejected for further participation on the grounds below:

•Voluntarily quitting.

•Use of forbidden medication or treatment during the trial that might affect analysis of results.

•Early termination of the process based on the investigator’s judgment (in the case of misdiagnosis, development of severe complications, and so on.).

•Failure to keep the patient blinded, or deblinding in case of emergency.

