### Interventions

Participants randomized to the treatment group will be administered SYKFT 2.4 g three times daily plus irbesartan 0.15 g once daily for 16 weeks. Those in the control group will receive SYKFT placebo 2.4 g three times daily in addition to irbesartan 0.15 g once daily for 16 weeks. Both groups will receive behavioral intervention and health education such as diet instructions. All test drugs, that is SYKFT, the placebo and irbesartan (trade name: Anbowei in Chinese pinyin) are manufactured by Tianjin Tongrentang Pharmaceuticals.

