### Sample size calculation

This is an exploratory phase II clinical study designed to provide evidence and a scientific rationale for advancing the treatment regimen into a phase III confirmatory study. The planned sample size is 80, with 40 in each treatment group.

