### Efficacy assessment

All primary analyses for this study will strictly follow the intention-to-treat (ITT) principle. The full analysis set (FAS) population, which will include randomized subjects who have received treatment at least once, will be used for primary efficacy outcomes analysis. In addition, a per-protocol analysis will be performed on the secondary outcomes. The per-protocol set (PPS) population will be restricted to patients who are compliant with the treatment protocol and have a completed CRF. Good compliance indicates the drug actually taken equals 80 to 120 percent of the required dosage. Missing values will be replaced using the last observation carried forward (LOCF) method.

Continuous variables will be described as mean ± standard deviation, and dichotomous data will be reported as percentages. A two-tailed test will be applied. Statistical significance will be defined as *P* <0.05 and 95% confidence interval will be calculated. Heterogeneity between groups will be tested at baseline.

The main analysis will be a comparison between the two groups concerning the proportion of patients achieving different levels of recovery (FR, GR, MR or NR) in terms of TCM symptoms and clinical biomarkers using the Wilcoxon rank sum test. In addition, the ORR will be compared between the two arms using the center-stratified Cochran-Mantel-Haenszel (CMH) method. For secondary outcomes, all continuous data will be analyzed via analysis of covariance adjusted for clinical center and baseline. Analyses of binary data will be based on logistic regression models.

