## Discussion

SYKFT is an improved version of the herbal prescription based on the valuable therapeutic knowledge of the late TCM practitioner Zhao Enjian, who had enjoyed nationwide fame for treating patients with chronic nephritis [10]. The formula is a combination of 11 herbal ingredients with a synergic effect of tonifying qi and yin, nourishing the kidney and spleen and detoxicating the body [11]. The tablet formulation is manufactured by Tianjin Tongrentang Pharmaceuticals (Register No: Z10940034) and film-coated tablets are now available for diabetes patients [10]. SYKFT is recommended for treating a variety of indications including fatigue, waist pain, swollen face and limbs, dizziness, tinnitus, proteinuria and hematuria.

Preclinical study evidences that SYKFT has curative effects on streptozotocin-induced diabetic rats with unilateral nephrectomy [12]. Another research study finds the drug’s renoprotective effect is associated with the upregulation of podocalyxin expression in DN mouse models [13]. The chronic toxicity test with an observation period of six months reported no death and no abnormal pathological changes in the experimental animals [unpublished data, Tianjin Institute of Medical and Pharmaceutical Science]. Also, SYKFT has been reported to have improved symptoms, controlled proteinuria and retarded the progression of renal failure for DN patients in clinical observations and preliminary trials [14-22].

In view of the current evidence base, we have designed this placebo-controlled RCT to test the efficacy and safety of SYKFT for diabetic nephropathy patients with qi-yin deficiency syndrome. The findings of this study will inform hypothesized effects of SYKFT and may provide an alternative treatment option for diabetic nephropathy. It will also provide evidence and a scientific rationale for advancing the treatment regimen into a phase III confirmatory study.

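### Prior ACE-inhibitor or ARB use is recorded at screening, but no analysis described in the article uses it; SI versus PI stays unbiased, but some precision is lost and absolute recovery rates depend on an unknown patient mix

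*Protocol article*

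**What the plan says.** Background: "angiotensin-converting enzyme inhibitors (ACEIs) or angiotensin receptor blockers (ARBs), are recommended renoprotective medications for DN sufferers".

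Interventions: both arms take the same irbesartan. For the control arm, "Those in the control group will receive SYKFT placebo 2.4 g three times daily in addition to irbesartan 0.15 g once daily for 16 weeks".

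The section on forbidden drugs and concomitant treatments states: "Use of any other Chinese medicine or western therapy like ACEIs or ARBs to relieve symptoms of diabetic nephropathy ought to be strictly prohibited". The related withdrawal ground concerns forbidden drugs taken during the trial. The inclusion and exclusion lists set no condition on earlier ACE-inhibitor, ARB, Chinese-medicine or SYKFT use. The Discussion says of SYKFT that "film-coated tablets are now available for diabetes patients".

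Table 1 records medical and drug-use history at Visit 1 (week -2). It also marks drug distribution at week -2, and drug recycling and drug count at week 0, where randomisation takes place. The text does not say what is dispensed at week -2.

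Randomisation is stratified by centre. Under Efficacy assessment, the main Wilcoxon rank sum test of recovery category names no covariate and the CMH test of ORR is stratified by centre. For secondary outcomes "all continuous data will be analyzed via analysis of covariance adjusted for clinical center and baseline", and binary data go to logistic regression.

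**The concern.** A patient whose first ARB is the study irbesartan may show a fall in proteinuria from that drug alone. A patient switched from another ACE inhibitor or ARB starts from a baseline that may already be lowered and has less left to gain. Two equal baseline values can therefore mean different things, and adjusting for baseline does not separate them.

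The recovery scale is sensitive to this. It classifies patients by percentage change, and any fall short of 40% still counts as modest recovery and enters the ORR.

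Two things are at stake. Variation due to prior use stays in the error term, although the variable that would remove it is already collected. And the ORR within each arm moves with the mix of prior users, which matters because the article presents the trial as the basis for a phase III study, whose planning could draw on the control rate.

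**Working it through.** **Inputs from the article.** "The planned sample size is 80, with 40 in each treatment group". "A two-tailed test will be applied", at P < 0.05. Five centres. No power, effect size or standard deviation is given for the 80, so there is no sample-size figure to reproduce.

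**Assumed (not in the article).** Share of prior users 30, 50 or 70%. Irbesartan lowers both urine markers by 30% in naive patients and 0% in prior users. Within-person CV is 30 to 50%, log changes are normal, their correlation between the two markers is 0.7, and SYKFT has no effect. A fall in either marker counts.

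**1. Bias.** Simulation of 40,000 trials per scenario, ignoring centre, gave a mean SI-PI difference of 0.00 under no effect and 0.20 under a true 20 points. Type I error without stratification was 0.048 to 0.058.

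**2. Chance imbalance.** SD of the between-arm difference in prior-use share, at 50%: √(2 × 0.5 × 0.5/40) = 0.112 (exact hypergeometric 0.113). The 95% range is ±1.96 × 0.113 = ±22 points; at 30% or 70% it is ±20 points.

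**3. Recovery by prior use.** SD of log change = √(2 ln(1 + CV²)), which is 0.415 at CV 30% and 0.668 at CV 50%. The probability that at least one marker passes the threshold is:

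| | CV 30%: naive / prior | CV 50%: naive / prior |
|---|---|---|
| any fall | 0.891 / 0.627 | 0.812 / 0.627 |
| fall ≥ 40% | 0.473 / 0.166 | 0.532 / 0.315 |

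The gaps are 0.264 and 0.185 for any fall, and 0.307 and 0.217 for a fall of 40% or more. A 95% imbalance then shifts the arm difference by 0.221 × 0.185 = 0.041 to 0.221 × 0.307 = 0.068, or about ±4 to ±7 points. Total sampling error is 1.96 × √(2p(1 - p)/40): ±22 points at p = 0.50 and ±19 at p = 0.76. The shift is already part of that error.

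**4. Precision of the continuous analysis.** With half prior users, the variance of log change due to prior use is 0.25 × (ln 0.7)² = 0.0318. The remaining variance is 0.1724 (CV 30%) or 0.4463 (CV 50%). Share due to prior use: 0.0318/(0.0318 + 0.1724) = 16%, and 0.0318/(0.0318 + 0.4463) = 7%. Removing it narrows a confidence interval by 1 - √(1 - 0.16) = 8%, or 1 - √(1 - 0.07) = 4%. These shares are before baseline adjustment.

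**5. Level of the control ORR.** With the any-fall rates above, going from 30% to 70% prior users:
- CV 30%: 0.7 × 0.89 + 0.3 × 0.63 = 81%, falling to 0.3 × 0.89 + 0.7 × 0.63 = 71%.
- CV 50%: 0.7 × 0.81 + 0.3 × 0.63 = 76%, falling to 0.3 × 0.81 + 0.7 × 0.63 = 68%.
- With a wider assumed gap of 80% versus 40%: from 68% to 52%.

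**6. Stratifying the ORR test.** By prior use alone, with a true difference of 20 points, power rose by about 1 to 10 points (smallest 0.472 to 0.484, largest 0.594 to 0.698). The largest gain comes from a scenario in which every naive SI patient recovers (80% + 20 points). The planned CMH test already uses centre, however. Crossing gives 5 × 2 = 10 strata of 80/10 = 8 patients on average, and simulated power went from 0.56 to 0.54, 0.47 to 0.46, 0.82 to 0.78 and 0.69 to 0.71.

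**The case against.** A reader might infer that recovery in this trial largely reflects who was ARB-naive at entry, and that the comparison is confounded. The article does not support that. Both arms receive the same irbesartan and allocation is randomised, so any start-up effect falls on both arms alike in expectation. Chance imbalance behaves as it does for every other unstratified prognostic factor and is covered by the standard error. The inference fits only the recovery level within an arm.

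It is also fair to say that every quantity driving the sizes above is assumed, that the trial is exploratory, and that the analysis plan, which is not shown, may already include this covariate. A journal article may likewise leave washout detail to the full protocol. And if whatever is dispensed at week -2 affects proteinuria, the gap between naive and prior users at week 0 could differ from the one assumed.

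A further tempting reading is that recent SYKFT users dilute the contrast. Market availability shows that such patients could enrol, not that they will, and no size can be given.

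What stands is narrower. A likely predictor is collected and is not among the covariates the article names, and the printed eligibility, forbidden-drug and visit-schedule passages do not together say how prior users reach the baseline urine.

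**Conclusion.** This is a low-cost improvement, not a flaw in the validity of SI versus PI. Expected bias is zero. Under the stated assumptions, with half the patients prior users, including prior use removes about 7 to 16% of the variance of log change in urine albumin. The control ORR could differ by roughly 8 to 10 points between a 30% and a 70% share of prior users, and by 16 points under the wider assumed gap. These figures scale with the unknown prior-use share and response rates. If prior users and naive patients respond alike to irbesartan, nothing is gained and almost nothing is lost.

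**What to change.** - Before unblinding, define prior ACE-inhibitor or ARB use (yes/no) from the Visit 1 drug history. Add it as a covariate to the ANCOVA and logistic models.
- Report recovery categories and ORR by prior use within each arm.
- Leave the Wilcoxon and centre-stratified CMH tests as planned, and do not cross prior use with centre in the CMH test: the strata become sparse and little or no power is gained at the rates examined. Crossing would pay only if the gap in recovery were much wider than the model above gives. A logistic or proportional-odds model of recovery category, adjusted for centre and prior use, can be a supportive analysis; its odds ratio is conditional on those factors.
- Separately, the sponsor should reconcile the eligibility lists, the forbidden-drug rule and Table 1 on how prior ACE-inhibitor, ARB, Chinese-medicine and SYKFT users are handled before the baseline urine, and state what is dispensed at week -2. The content of that rule is for the sponsor to set.

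The analysis change costs one derived variable, one degree of freedom per model and one extra table. It needs no new data and no change to randomisation, which had already begun (20 patients by March 2013).

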### Measurement items and time points of data collection

Relevant examinations will be performed and patient data will be collected at 2 weeks before baseline, at baseline, at 2 weeks post baseline and every 4 weeks from 4 to 16 weeks during treatment. Items to be measured and the time points of data collection can be found in Table 1.

**Table 1 T1:** Measurement items and point of data capture

	**Screening**	**Baseline**	**Treatment**				
	**Visit 1**	**Visit 2**	**Visit 3**	**Visit 4**	**Visit 5**	**Visit 6**	**Visit 7**
**Items**	**−2 weeks**	**0 weeks**	**2 weeks**	**4 weeks**	**8 weeks**	**12 weeks**	**16 weeks**
Informed consent form	X						
Inclusion/exclusion criteria	X						
Demographic information	X						
Medical/drug use history	X						
Concomitant disease and treatment	X						
General physical examination	X						
Combined medication	X	X	X	X	X	X	X
Vital signs	X	X	X	X	X	X	X
TCM symptom	X	X	X	X	X	X	X
Urine protein test	X	X	X	X	X	X	X
Routine urine test	X	X	X	X	X	X	X
Renal function (SCR, BUN, GFR) Serum albumin	X	X	X				X
Routine blood test	X	X					X
Stool routine test and fecal occult blood test	X	X					X
Liver function (ALT/AST/GGT/TBIL/ALB)	X	X					X
Blood electrolytes	X	X	X				X
Blood coagulation (TT/APTT/PT/FIB)	X	X					X
Blood glucose	X	X	X	X	X	X	X
Glycosylated hemoglobin	X	X			X		
Electrocardiogram (EGG)	X	X					X
Adverse events	X	X	X	X	X	X	X
Randomization		X					
Drug distribution	X	X	X	X	X	X	
Drug recycling		X	X	X	X	X	X
Drug count		X	X	X	X	X	X
Research conclusion							X

X: Have indicators tested in the specific time period. ALB, serum albumin; ALT, alanine aminotransferase; APTT, activated partial thromboplastin time; AST, aspartate aminotransferase; BUN, blood urea nitrogen; FIB, fibrinogen; GFR, glomerular filtration rate; GGT, gamma-glutamyl transpeptidase; PT, prothrombin time; SCR, serum creatinine; TBIL, total bilirubin; TCM, traditional Chinese medicine; TT, thrombin time.

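### The withdrawal and exit rules do not separate stopping study treatment from ending follow-up, so a primary analysis described as strictly intention-to-treat would rest partly on carried-forward values instead of observed week-16 outcomes

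*Protocol article*

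**What the plan says.** The rule stands in the protocol article under 'Concomitant treatments and forbidden drugs': "Patients will be withdrawn or be rejected for further participation on the grounds below". Besides voluntary quitting, it lists three grounds:

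- "Use of forbidden medication or treatment during the trial that might affect analysis of results"
- "Early termination of the process based on the investigator’s judgment", with misdiagnosis and severe complications as examples
- "Failure to keep the patient blinded, or deblinding in case of emergency"

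The next section, 'Exit criteria corresponding to treatment failure', adds uncontrolled blood pressure, HbA1c above 59 mmol/mol, uncontrolled blood glucose and persistently elevated proteinuria. It does not say whether an exit ends treatment, follow-up or both.

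'Measurement items and time points of data collection' schedules examinations before and at baseline, at week 2 and "every 4 weeks from 4 to 16 weeks during treatment". Table 1 has no column for a visit after withdrawal.

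On analysis, 'Efficacy assessment' states: "All primary analyses for this study will strictly follow the intention-to-treat (ITT) principle". The full analysis set (FAS), "which will include randomized subjects who have received treatment at least once, will be used for primary efficacy outcomes analysis". For gaps in the data: "Missing values will be replaced using the last observation carried forward (LOCF) method".

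**The concern.** What the first list ends is participation, not study drug. Voluntary quitting can genuinely end data collection. The other three grounds need not, because the patient may still be willing and able to give a week-16 urine sample. A site applying the sentence as written would most naturally stop the visits.

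The three grounds and the treatment-failure exits all occur after randomization, and they may be related to treatment arm or to outcome. An intention-to-treat comparison depends on seeking outcomes from randomized patients whatever treatment they took. If follow-up ends at these events, the patients stay in the denominator but their week-16 result is a substitute. The issue is the decision not to collect data that could be collected. It would remain whichever imputation method was used.

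**Working it through.** The plan has no figure of its own to reproduce on this point. 'Sample size calculation' gives 80 patients, 40 per arm, with no effect size, power or dropout rate. The check is therefore a reading of the text, followed by an illustration of scale.

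**Step 1. Does a removed patient stay in the analysis?** Yes. Anyone randomized and treated at least once is in the FAS, and neither list removes a patient from it.

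**Step 2. Which value is analysed?** If visits end at removal, there is no week-16 measurement, and LOCF supplies the last earlier one. Table 1 schedules urine protein and TCM symptoms at weeks 0, 2, 4, 8, 12 and 16, so the substitute comes from week 12 at the latest and possibly from much earlier.

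**Step 3. How is that value scored?** Under 'For laboratory indicators of the disease', a decrease of at least 40% in either urinary measure is good recovery, a decrease below 40% is modest recovery, and only unchanged or worsened results are no recovery. The formula is

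ORR = (full + good + modest) / group size.

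For the laboratory measures, the line between success and failure is therefore zero change. Consider a patient with a small fall at week 4 who then takes a forbidden drug because the disease is worsening and is removed before the next sample. That patient carries the week-4 fall to week 16 and counts as a success. The TCM score is less exposed, because it needs a reduction of at least 30% to leave the no-recovery category.

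**Step 4. Scale, on assumed removal rates.** Let n = 40 per arm, d the assumed proportion removed (the same in both arms), m = 40 × d, and s the observed successes in an arm.

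- True ORR in an arm lies between s/n and (s + m)/n.
- The difference between arms A and B lies between (s_A − s_B − m)/n and (s_A − s_B + m)/n, that is, plus or minus m/n around (s_A − s_B)/n.

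| Assumed d | m per arm | Total of 80 | Bound on ORR difference | Full span |
|---|---|---|---|---|
| 5% | 2 | 4 | ±5 points | 10 points |
| 10% | 4 | 8 | ±10 points | 20 points |
| 15% | 6 | 12 | ±15 points | 30 points |
| 20% | 8 | 16 | ±20 points | 40 points |

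Each patient kept under observation narrows the full span by 1/40 = 2.5 points.

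**Step 5. Is lost power the main harm?** No. With assumed ORRs of 60% and 80%, power is 49.7% at 40 per arm and would be 41.3% if only 32 per arm were analysed (d = 20%). The plan keeps all treated patients through LOCF, so the harm lies mainly in possible bias from substituted values.

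**The case against.** The strongest reply is that no patient is excluded from the primary analysis and that the loss of data is inferred. Nowhere does the article say that visits stop, and it may be condensing a full protocol that provides follow-up after withdrawal. The first part is correct and limits the point: the conflict is with observing outcomes, not with who is analysed. The second part weakens it only partly. The article does not merely omit follow-up; it states a rule ending participation, and a full protocol that continued the visits would still have to be reconciled with that sentence.

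A reader might infer several stronger things that the documents do not support:

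- **That removed patients vanish from the primary analysis.** The FAS definition keeps them once they have had a dose.
- **That unblinding ends follow-up of the adverse event behind it.** 'Reporting of adverse events' asks for duration, actions taken and results without exempting withdrawn patients, and the safety set keeps everyone with at least one visit.
- **That any forbidden drug leads to removal.** The ground is limited to use that might affect the results.
- **That removal favours a particular arm.** Differential use of added treatment or differential unblinding is plausible, but the documents give neither rate nor direction.

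It is also fair to say that the bounds above are worst cases, ignore the measurements taken before removal, and would apply to missing data from any cause. They show scale and are not a forecast. The study's exploratory label lowers the stakes but does not remove them, since its results are meant to justify a phase III study.

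**Conclusion.** The point holds in a limited form and should be corrected. The withdrawal grounds and the treatment-failure exits do not separate stopping treatment from ending follow-up. Followed as written, they replace obtainable week-16 outcomes with earlier values for treated patients who remain in the FAS, which undercuts the stated strict intention-to-treat analysis. The laboratory ORR is the most exposed measure, because any fall counts as recovery.

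The size is unknown. On the sole assumption of 5–20% removal in each arm, the ORR difference is undetermined by plus or minus 5–20 percentage points in the worst case. The conclusion also assumes that sites read the end of participation as the end of visits. That is the natural reading, but the article does not spell it out.

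**What to change.** Reconcile 'Concomitant treatments and forbidden drugs', 'Exit criteria corresponding to treatment failure' and 'Efficacy assessment' by adding a statement to this effect:

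- Except after withdrawal of consent or loss to follow-up, a patient who meets any of the listed grounds or exit criteria continues the remaining Table 1 visits to week 16, at least for urine protein, TCM score and adverse events.
- The reason and date are recorded.
- Observed values are analysed in the arm to which the patient was randomized.

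The change concerns data collection only. When treatment is stopped is left as it is.

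The cost is small. The visits are already scheduled, so no new procedure is needed, but sites would continue to see a few patients who may be off study drug, and some week-16 values would reflect other treatment. The wording amendment needs approval from the review boards of the participating hospitals. With 20 of the planned 80 patients randomized by March 2013, 60 were still to be enrolled at that date and could be covered in full.
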